**Figure 2 BMJOPEN2015010682F2:**
[figure not shown]
Study design. DCE, discrete choice experiment.

### Stage 1: formative phase—development and piloting of choice tasks, attributes and levels

A thematic analysis of qualitative data gathered in an earlier study^29^ led to the identification of key attributes which were important to the respondents' choice of a HIV prevention product. These will be explored in the context of more recent literature to account for evolution in the HIV prevention field, for example, changes in technology (eg, product efficacy) and policy (eg, potential for free provision by the South African Government). Then, between 5 and 10 ‘pre-pilot’ interviews will be carried out in each population to assess participants' understanding of background questions and DCE choice tasks, explore the most meaningful representations of attributes and levels, and identify any issues with the tablet-based implementation of the DCE. The pre-pilot stage will be critical in creating clear, relevant and realistic choice sets which are presented to participants in an understandable manner. The DCE to be piloted is unlabelled, meaning all products will not be presented at once, but each will appear as an available alternative according to the experimental design. The six attributes of the DCE and their levels are shown in table 1.

**Table 1 BMJOPEN2015010682TB1:** Attributes and levels

Attribute	Levels
Product	Oral pre-exposure prophylaxis, microbicide gel, microbicide gel with SILCS diaphragm, vaginal ring, injectable pre-exposure prophylaxis
HIV protection	55%, 75%, 95%
Pregnancy prevention	Prevents pregnancy, does not prevent pregnancy
Frequency of use*	Every time you have sex, once per day, once per week, once per month, once per 3 months, once per 6 months, once per year
Protection against other STIs	Protects against other STIs, does not protect against other STIs
Side effects (probability of occurrence fixed)	Stomach cramps/pain, nausea/feeling sick, dizziness, none

*As no product can be used at all frequencies, the design will contain constraint terms where only relevant frequencies will be presented alongside products. Frequencies were chosen to be informative for product development: oral PrEP—daily, weekly, monthly; microbicide gel—coitally; SILCS diaphragm and microbicide gel—coitally, daily; vaginal ring—weekly, monthly, three-monthly, six-monthly; injection—three-monthly, six-monthly, annually.

SILCS; STI, sexually transmitted infections.

We will include five new prevention products, chosen to reflect the range of potential ARV delivery mechanisms. Some (eg, oral PrEP) are fully developed and are in the later stages of global licensing, while others (eg, injectables) are a few years from efficacy trials and potential roll-out. Women will be presented with the full range of products, while men will only be presented with male-initiated options (ie, oral PrEP and injectables). We include two products based on microbicide gels, despite recent unsuccessful effectiveness trials.^6^
^9^ Trial results suggest that gels were efficacious when used adherently, however, many participants were not able to use the products consistently enough as part of everyday life. Including these products in the DCE will allow us to explore how preferences for products vary by characteristics, such as frequency of use and potential side effects, and provide an opportunity to compare DCE predictions to reality. We note that common side effects were chosen through reports from PrEP trials and ART regimens using ARV drugs.^34^
^35^

FGDs will be carried out with FSWs, as the risk factors and sexual relationships of this group are likely to be substantively different from other population, while it was noted that there was a gap in the literature and in local knowledge on FSW preferences. It is a limitation of this study that we are unable to carry out FGDs with men or adolescent women; however, we will use the expertise and experience of local collaborators alongside identifying substantive literature to assess relevant attributes for these groups. In the FSW FGD, themes related to HIV prevention choices and negotiation of protection with clients and partners will be explored in four FGDs with between 8 and 12 participants in each. The qualitative data from the focus groups will then be analysed using thematic analysis to inform the final version of the DCE survey tools.^36^ These discussions will provide novel insights into decision-making by FSWs around HIV prevention which have never been explored in a DCE context before.

The DCE will be piloted through an initial fractional factorial design which will be generated by specialist NGENE software^37^ and tested face to face with a subsample of 20 respondents, five from each population group (men, women, adolescent girls and FSWs). These pilots will aim to assess how well respondents understand questions and responses, whether tablet-based enumeration is feasible and reliable, and explore different presentations of DCE tasks and attributes. Furthermore, the responses from these DCE tasks will be analysed using a multinomial logit model (MNL) to obtain point estimates of utility function parameters. These estimates will be used in generating a statistically efficient design for the final DCE.

The attributes and levels shown above yield 1260 possible product profiles, far too great a number to present to all participants. Recent advances in DCE design have led to the development of ‘efficient’ designs which, when informed by prior information from a pilot study and/or the literature, offer more reliable parameter estimates when compared with traditional orthogonal designs. To ensure realistic choice data and avoid overestimating demand for new products,^32^ participants can opt out of choosing a new product with a fourth alternative presented of ‘do what I did last time’ (ie, use a condom or nothing). Since an unlabelled design is used to reduce the number of choices within a set from six to four, it is likely (and certain in the male DCE) that some products will be presented twice in the same choice set, with different attribute levels. Interviewers will be fully trained to explain this nuance to participants.

Finally, data will be captured in the final questionnaire on salient background characteristics of participants including: age, gender, quality of life, reproductive history, relationship history and HIV knowledge. This data will allow the analysis of how preferences are shaped by life circumstances, for example, if a respondent is seeking to conceive with a partner. Through framing choice tasks around the last sex act, we will be able to explore how preferences may vary by partner type, for example, between non-commercial and commercial partners of FSWs, or between long-term and short-term sexual relationships. Data will also be gathered on the gender of respondents' most recent sexual partner. The piloting process will inform which characteristics should be included in final data analysis as explanatory variables for preferences in HIV prevention products. Finally, we note that while trials of some products (oral PrEP and a vaginal ring) will be ongoing in some populations in South Africa during this study,^38^ the geographically concentrated and research-naive populations chosen for this work are very unlikely to have experience of using these (eg, through participation in trials). We will record if participants have prior experience of using any of these products.

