### Stage 2: administration of DCE

#### Participants and recruitment

The survey and DCE will be administered using Open Data Kit (https://opendatakit.org/) software on tablet computers. The acceptability and feasibility of tablet-based data collection will be assessed during the formative stage, although it is expected that it will minimise missing data, and reduce laborious data entry and cleaning.^39^
^40^ Participants will be given a ZAR 50 (GBP £2.50) voucher as compensation for their time. Participants will be asked to self-report their HIV status, and we aim to maximise accuracy in reporting through careful confidentiality and sensitivity training of the interviewer team, which has considerable experience in collection of HIV and sexual health data.

To ensure that choices are relevant and meaningful to participants, three steps will be taken to maximise the realism of choice scenarios. First, all interviewers will be equipped with a full set of example products: a real SILCS diaphragm, alongside placebo PrEP tablets (similarly coloured, shaped and sized), vaginal rings, microbicide gels and injections (an empty syringe). Participants will be encouraged to touch and explore the products as much as they wish before beginning choice tasks. Second, interviewers will be thoroughly trained and tested on how to describe products to participants. In addition, concise and clear information sheets will be used when explaining the tasks, products and attributes. Third, the statistical design of the DCE will be such that only relevant products are presented to different groups, and relevant attributes for different products. For example, only injectable and PrEP options will be presented to men, while the frequency of injections will be restricted to between once per month and once per year.

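### In the male choice experiment, the Table 1 footnote leaves oral PrEP and injections with no shared frequency, so with categorical frequency the product effect is aliased with the between-product frequency difference; the Stage 2 text gives a different injection range

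*Protocol article*

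**What the plan says.** The protocol article describes the male experiment in two places.

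- **Stage 1 (formative phase), Table 1 and its footnote.** Frequency of use has seven levels: "Every time you have sex, once per day, once per week, once per month, once per 3 months, once per 6 months, once per year". The footnote restricts them by product: "the design will contain constraint terms where only relevant frequencies will be presented alongside products". For the two products that matter here it lists "oral PrEP—daily, weekly, monthly" and "injection—three-monthly, six-monthly, annually". The text after the table limits men to oral PrEP and injectables.
- **Stage 2, Participants and recruitment.** The restriction on products is repeated: "only injectable and PrEP options will be presented to men". The same sentence then says that "the frequency of injections will be restricted to between once per month and once per year".

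The Abstract makes the importance of product attributes the second aim. Stage 3 (data analysis) promises marginal rates of substitution between attributes and names the model families. It does not say whether frequency enters as categories or as a continuous interval, nor whether men are modelled separately.

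**The concern.** Product and frequency are two of the six attributes. To separate their effects without further assumptions, at least one frequency must appear with both products. Under the footnote none does for men: every oral PrEP profile is used monthly or more often, and every injection profile three-monthly or less often.

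Suppose that men mostly choose injections. The data could not then show whether they like injections as such or like less frequent use. That question bears directly on the second aim and on any trade-off that involves product type. More men would not help, because the limit lies in which profiles are shown.

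The Stage 2 sentence makes the point less settled. On its natural reading it admits a monthly injection, and that single level would link the two products. So the article leaves open whether the male model with separate terms is identified.

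**Working it through.** **Inputs, all from the article**

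- Products for men: oral PrEP and injection.
- Oral PrEP frequencies (footnote): daily, weekly, monthly.
- Injection frequencies (footnote): three-monthly, six-monthly, annual.
- Injection range (Participants and recruitment): once per month to once per year.
- An opt-out alternative in each choice set.

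The coding of frequency is not stated, so I checked categorical coding first and continuous coding second. The plan gives no figure of its own to reproduce here.

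**1. Male design under the footnote, categorical frequency**

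Write the utility of a new product relative to opt-out, other attributes held fixed, as

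U(product, frequency) = α + β·[injection] + γ(frequency), with γ(daily) = 0.

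- Pairs shown: 3 + 3 = 6.
- Parameters: 1 constant + 1 product + 5 frequency = 7.
- On every row, [injection] = [three-monthly] + [six-monthly] + [annual]. On opt-out rows, both sides are 0.
- Rank is therefore 6 of 7.

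Equivalently, add any δ to β and subtract δ from γ for the three injection frequencies: all six utilities are unchanged, so no choice data can tell the two versions apart.

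With the other four attributes added (six more columns: HIV protection linear 1, pregnancy 1, other STIs 1, side effects 3), the multinomial logit information matrix has 7 + 6 = 13 parameters and rank 12. This used three new-product alternatives plus opt-out, random choice sets and equal choice probabilities. Still exactly one degree of freedom is lost.

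**2. What is and is not estimable in that design**

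| Quantity | Estimable? |
|---|---|
| Weekly vs daily, monthly vs daily (within oral PrEP) | yes |
| Six-monthly vs three-monthly, annual vs three-monthly (within injection) | yes |
| Each of the six pairs against opt-out | yes |
| Three-monthly injection vs monthly oral PrEP, as whole profiles | yes |
| HIV protection, pregnancy, other STIs, side effects | yes |
| Injection vs oral PrEP as a product effect | no |
| Three-monthly vs monthly, or vs daily, as a frequency effect | no |

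The fourth row shows the structure. That difference equals β + γ(three-monthly) − γ(monthly). The sum is identified; its parts are not.

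**3. If a monthly injection were shown**

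Pairs: 3 + 4 = 7. Parameters: 7. Rank: 7, and the full information matrix has rank 13 of 13. The monthly level then appears with both products, so β is the difference between them at that level.

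**4. Female design under the footnote**

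Pairs: oral PrEP 3 + gel 1 + gel with diaphragm 2 + ring 4 + injection 3 = 13. Parameters: 1 + 4 + 6 = 11. Rank: 11, so nothing is aliased. The ring supplies the link, because "vaginal ring—weekly, monthly, three-monthly, six-monthly" overlaps with both oral PrEP and injection.

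**5. Male design under the footnote, continuous frequency**

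One slope replaces five frequency terms: 3 + 6 = 9 parameters, rank 9. With intervals of 1, 7, 30.4, 91.3, 182.6 and 365 days and equal weight on the six pairs:

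- log interval: correlation with product 0.848, variance inflation 1/(1 − 0.848²) ≈ 3.6;
- linear interval: correlation 0.777, variance inflation 1/(1 − 0.777²) ≈ 2.5.

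Both effects can be fitted, but the split between them rests on the assumed shape of the curve across the gap from monthly to three-monthly.

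**The case against.** **The analysis model is not specified.** The article fixes neither dummy coding nor a separate male model, and a condensed article may leave that to the analysis plan. This stands: the aliasing is conditional on categorical frequency in a male model. But the alternatives supply an assumption where the design supplies no data. A continuous term assumes a functional form. Pooling assumes that men share women's frequency effects, although the Sample size section expects to explore differences between groups.

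**The Stage 2 sentence is an example that gives bounds, not levels.** All three footnote frequencies for injection lie inside those bounds. This stands in part. The sentence does not say that a monthly injection will be shown, so it cannot be counted as a second level list. Its lower bound is nevertheless a Table 1 level that the footnote does not give for injections, and the difference decides whether the model is identified.

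**The levels are not final.** Table 1 describes the experiment to be piloted, and the final design follows the pilot. True, and this makes the correction cheap. It does not show that anyone will look for the problem.

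**Uptake can still be predicted.** Correct for every pair that the footnote allows men to see.

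A reader might go further and infer that product and frequency are completely confounded, that neither can be estimated in men, or that the second aim fails for men. The documents do not support this. Frequency is nested within product, one contrast is lost, and four of the six attributes are untouched. Trade-offs such as efficacy against frequency can be computed within each product.

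**Conclusion.** The point holds in a limited form. If the footnote is followed and frequency is categorical in a male model, one degree of freedom is lost: the product effect cannot be told apart from the between-product frequency difference. This concerns 200 of 800 respondents (25%). No male response is wasted, because all six pairs can be valued against opt-out; what is lost is one interpretation of those values.

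That interpretation matters for the second aim and for any marginal rate of substitution that involves product type in men. It does not threaten the female design, nor male uptake predictions for the pairs shown.

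The two descriptions of injection frequency also disagree on their natural reading and must be reconciled. The documents do not settle which is intended. The issue should be fixed, but it is not fatal.

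**What to change.** 1. Before the final design is generated, reconcile the Table 1 footnote with the injection range in Participants and recruitment, so that one list of admissible frequencies governs the male design. Which list applies is for the investigators to decide.
2. Write down the intended male utility function, including how frequency is coded, and check that the male design matrix has full rank for it.
3. If the two frequency sets stay disjoint, model men with one six-level product-by-frequency factor, and state that separate product and between-product frequency effects are not estimated in men. Alternatively, state the functional-form or pooling assumption that separates them, and report the separated effects as dependent on it.

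The cost is a line in the design constraints and a line in the analysis text, with no extra participants. The downside is either one more admissible profile or a slightly narrower claim for men.

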### Stage 2: administration of DCE

#### Participants and recruitment

The survey and DCE will be administered using Open Data Kit (https://opendatakit.org/) software on tablet computers. The acceptability and feasibility of tablet-based data collection will be assessed during the formative stage, although it is expected that it will minimise missing data, and reduce laborious data entry and cleaning.^39^
^40^ Participants will be given a ZAR 50 (GBP £2.50) voucher as compensation for their time. Participants will be asked to self-report their HIV status, and we aim to maximise accuracy in reporting through careful confidentiality and sensitivity training of the interviewer team, which has considerable experience in collection of HIV and sexual health data.

To ensure that choices are relevant and meaningful to participants, three steps will be taken to maximise the realism of choice scenarios. First, all interviewers will be equipped with a full set of example products: a real SILCS diaphragm, alongside placebo PrEP tablets (similarly coloured, shaped and sized), vaginal rings, microbicide gels and injections (an empty syringe). Participants will be encouraged to touch and explore the products as much as they wish before beginning choice tasks. Second, interviewers will be thoroughly trained and tested on how to describe products to participants. In addition, concise and clear information sheets will be used when explaining the tasks, products and attributes. Third, the statistical design of the DCE will be such that only relevant products are presented to different groups, and relevant attributes for different products. For example, only injectable and PrEP options will be presented to men, while the frequency of injections will be restricted to between once per month and once per year.

If participants choose an ARV-based, non-condom product, they will subsequently be asked whether or not, if the product was available, they would have used it the last time they had sex. If they indicate that they would, they will be asked whether they would have used it alongside, or instead of, a condom. This will enable us to ascertain whether new products will be used in combination with, or in substitute of, condoms. Since there is likely to be no additional benefit from dual use of ARV-based products, nor would medical advice suggest this would be something users should do, the DCE framework does not allow for the combination use of ARV-based products, except the SILCS diaphragm which is used in concert with gel.

Primary data will be collected in Ekhurhuleni Metropolitan Municipality, Gauteng Province. The Municipality was selected as the study site because it contains a broad range of residential contexts, representing a range of demographic, socioeconomic and cultural characteristics. We employ a proportional cluster sampling strategy, stratified by population. For the 200 men and 200 women, the nature of the household sampling method means that we may be able to interview both cohabiting partners in a relationship; assuming a sufficient number of individuals in cohabiting relationships are available and consent to participate, analysis of preferences within relationships would be a particularly novel element of this research.

Different enumeration teams will interview respondents from each group. For the general population, a specialist local data collection firm with over 20 years of experience, Progressus Research and Development (http://www.progressus.co.za/), will manage the survey process, generate the sampling design, and carry out the DCE. On finding an adult present in a household, the interviewer will identify him/herself, explain the study, and request permission to note down all women, men and adolescent girls living in the house ordered by age. We expect the whole survey, including DCE, will take around 30–45 min to complete.

Two hundred FSWs will be recruited through RDS. We will employ peer educators who will first locate sex work ‘hotspots’ in the Vosloorus area, before selecting 7–10 seeds among FSWs operating in different areas such that different social networks are reached (eg, FSWs working in brothels, on the street or in bars or taverns). These women will be invited to participate in the study and given a ZAR 50 (GBP £2.50) voucher as compensation for their time, before receiving three coupons containing the study information to distribute to colleagues. When one of these colleagues attend the study site, both they and their recruiter receive a small incentive in the form of a ZAR 20 (GBP £1) voucher. The amount of compensation was based on similar studies among FSWs in South Africa, and is designed to be high enough to compensate for potential loss of one client during study participation, but not so high as to encourage significant fraudulent enrolment.

#### Sample size

The DCE literature has not yet reached consensus on the best way to successfully estimate the sample size required in a DCE study to return meaningful, statistically robust parameter estimates. Applying the popular rule of thumb of Johnson and Orme,^41–43^ we estimate that a sample size of 90 should be sufficient to estimate parameters of the DCE structure shown in figure 1. Similarly, the literature suggests that between 20 and 30 observations per choice set can provide precise parameter estimates.^18^
^44^ This indicates that our sample size of 800 will be sufficient to estimate parameters over the entire population, as well as to explore any variations in preferences which might exist between groups.

